### **7.4 Criteria for Withdrawal/Discontinuation of Participants**

A limited number of dropouts among HPs and patients has been taken into account when assuming a censoring probability of 40% for sample size calculations (see section 11.2).

Any patient withdrawing his consent will be asked for reasons; individual follow up will be discontinued and his accumulated data will be evaluated in coded form. Patients revoking their consent will be replaced in the ongoing recruitment process while possible.

Discontinuation of participants due to safety reasons, failure of participants to adhere to protocol requirements, disease progression, or abrupt termination of the study intervention is not possible given that the intervention is one-time only and non-continuing.

## 8 STUDY INTERVENTION

### 8.1 General Information and Administration of Interventions

#### 8.1.1 Study Intervention

The intervention takes place on different levels with different target populations:

- a. *Teaching session (“Teach-the-Teachers”) for the senior HPs in charge of postgraduate training and supervision of the interns (assistant physicians)*

The purpose of this training of two hours duration is to integrate the discharge procedure (see below) into the daily work of the HPs during the study period. Consecutively, the senior HPs will teach the interns how to apply the structured discharge procedure. This will guarantee the consistency of the intervention even if the fluctuation among interns is high due to organized job rotations within hospitals.

The teaching session will address the following items:

- How to identify patients eligible (possibly in collaboration with nurses)
- How to handle the in- and exclusion criteria
- How to apply the medication review tool (discharge checklist in forms 5b and 5c, see list of study instruments in appendix 18.1) which has been previously tested (15, 32) to the medication plan of the patient before discharge by the HP
- How to involve the senior HP responsible for the interns’ supervision in the medication review, depending on the clinic’s/wards’ usual discharge procedures
- How to involve patients in the changes suggested by the HP
- How to create a discharge medication plan for the patient, after the decision is taken
- How to involve the GPs in the post-discharge phase. An offer for the GP to call the HP in order to discuss the medication plan is prepared on the discharge medication plan. This should guarantee a consensus between HP and GP in order to increase the GPs’ adoption of the changes suggested on the long term
- How to deal with the different data collection forms

- b. *The intervention at discharge*

The intern HP performs a critical review of the medication plan, supervised by his senior HP, discusses the results of this review and his suggestions with the patient and creates a discharge medication plan to be used by the patient. The patient is encouraged to consult his GP within seven days.

Furthermore, the intern HP communicates all medication changes (cessation of specific medication, change of dosage, introduction of new drugs) to the patient’s GP in written form, accompanied with an invitation to the GP to discuss any medication changes (forms 5b and 5c, see appendix 18.1).

To ensure correct and complete implementation of the discharge procedure the intern HP documents these steps in writing, using a specifically designed checklist (also to be found in forms 5b and 5c, appendix 18.1).

At present, the above mentioned CRFs are to be understood as samples, since the optimal data collection and transmission strategy at discharge will be worked out individually with each clinic in order to minimize the additional documentation workload of the HP.

### **8.1.2 Control Intervention**

The control group will receive “usual care”, meaning that the HPs will discharge all patients following the established discharge procedures of their respective clinics. In a two-hour presentation, a minimum of necessary information will be given to the participating HPs concerning multimorbidity as well as legal and organizational aspects of the study (eligibility of patients, informed consent, handling and disclosure of patient data).

## **8.2 Compliance with Intervention**

Patients are encouraged to consult their GPs within seven days after discharge but failure to do so is not considered to be in violation of the study regimen, as GP consultation is not mandatory. Therefore, no specific procedures are foreseen in such cases.

## **8.3 Data Collection and Follow-up for Withdrawn Participants**

In case of pending responses from patients at 1, 3 or 6 months after discharge the patients will be contacted by phone or in writing and invited to provide any missing data.

Any patient withdrawing his consent will be asked for reasons, and his accumulated data will be evaluated in coded form. Both the patients' right to withdraw consent at any point of time and the consequences thereof are explained in the patient information sheet.

## **8.4 Concomitant Interventions**

Patients may receive any drug or other therapy for any illness before and during the study, and no specific rules will prohibit any such treatment. All treatments will be documented in the patients' personal medical records as usual.

Personal, social, professional or economic circumstances that might affect a patient's state of health are captured globally within the QoL-questionnaires.

## 9 STUDY PROCEDURES

### 9.1 Study Flow Chart/Table of Study Procedures and Assessments

[figure not shown]

| Study Period                                 | HP Recruitment and Teaching |          | Hospital Stay   |               | Post Hospital Follow Up |                 |           | Eval. and Dissem. |
|----------------------------------------------|-----------------------------|----------|-----------------|---------------|-------------------------|-----------------|-----------|-------------------|
| Time Intervall                               | 01/2018-06/2018             |          | 03/2018-03/2019 |               |                         | 10/2018-12/2020 |           |                   |
| Point in Time (Months after Discharge)       |                             |          |                 | 0             | 1                       | 3               | 6         |                   |
| Study Stage                           | R                    | T | A        | D = T0 | T1               | T3       | T6 |                   |
| HP Recruitment                               | x                           |          |                 |               |                         |                 |           |                   |
| HP Information and Informed Consent          | x                           |          |                 |               |                         |                 |           |                   |
| Clinic Characteristics                       | x                           |          |                 |               |                         |                 |           |                   |
| Randomization                                | x                           |          |                 |               |                         |                 |           |                   |
| HP Teaching                                  |                             | x        |                 |               |                         |                 |           |                   |
| Patient Selection and In-/Exclusion          |                             |          | x               |               |                         |                 |           |                   |
| Patient Information and Informed Consent     |                             |          | x               |               |                         |                 |           |                   |
| Biometric Patient Data                       |                             |          | x               |               |                         |                 |           |                   |
| Medication Plan                              |                             |          |                 | x             |                         |                 |           |                   |
| Changes in Medication                        |                             |          |                 | x             |                         |                 |           |                   |
| Readmission with Date (if applicable)        |                             |          |                 |               | x                       | x               | x         |                   |
| ED Visits/GP Encounters                      |                             |          |                 |               | x                       | x               | x         |                   |
| ATC-Codes                                    |                             |          |                 | x             |                         |                 |           |                   |
| Number of Drugs                              |                             |          |                 | x             | x                       | x               | x         |                   |
| Quality of Life                              |                             |          |                 | x             | x                       | x               | x         |                   |
| Frequency of GP-HP Communication             |                             |          |                 |               | x                       |                 |           |                   |
| Time for Applying Intervention               |                             |          |                 | x             |                         |                 |           |                   |
| Dropout Rates                                |                             |          |                 |               | x                       | x               | x         |                   |
| Feasibility/Acceptance and Barriers/Enablers |                             |          |                 |               |                         |                 |           | x                 |
| Debriefing of Control HPs                    |                             |          |                 |               |                         |                 |           | x                 |
| Data Analysis                                |                             |          |                 |               |                         |                 |           | x                 |
| Final Reporting/Publication/Dissemination    |                             |          |                 |               |                         |                 |           | x                 |

Study stages: R = Recruitment, T = Teaching, A = Admission, D = T0 = Discharge, T1/2/3 = 1/2/3 months after discharge

## 9.2 Assessments of Outcomes

The assessment of all outcomes is laid out in sections 5.1-5.3 and 9.3. Additional details and all assessment tools can be found in the appendices.

### 9.2.1 Assessment of Primary Outcome

Possible readmission and the respective dates (or non-readmission, respectively) will be collected from the patients in writing at 1, 3 and 6 months after discharge using paper case report forms. In case of outstanding responses the study team will contact (in the following order) patients, relatives, GPs or hospitals by phone or in writing in order to complete the missing data.

### **9.2.2 Assessment of Secondary Outcomes**

Readmission rates will be calculated from primary outcome data, and the number of ED visits and GP encounters will be collected in the same way as the primary outcome data.

Patients will be requested to submit a copy of their current medication plans together with the completed QoL-questionnaires at discharge and after 1, 3, and 6 months to the study center, from which ATC-codes and the number of drugs will be compiled. Again, any attempt will be made to collect missing data by phone calls or in writing from patients, relatives, GPs and hospitals. This procedure will also capture deaths and dropout rates of patients.

Data regarding GP-HP contacts and communication before and after discharge and ratings of feasibility and acceptance will be collected from HP records and questionnaires. Semi-structured telephone interviews will be used to assess barriers and enablers of deprescribing among HPs and patients.

### **9.2.3 Assessment of Covariates**

Patient characteristics (sex, age) will be collected together with the patients' informed consent.

### **9.2.4 Assessment of Safety Outcomes**

#### **9.2.4.1 Serious Adverse Events**

For the definition of serious adverse events (SAEs) see section 10.1. Inpatient treatment and death are assessed within this study as primary or secondary outcomes, respectively, and will be recorded retrospectively.

### **9.2.5 Assessments in Participants who Prematurely Stop the Study**

Patients who withdraw their consent or prematurely stop the study for subjective reasons will remain in the care of their attending GPs. No further safety outcomes will be recorded within the study.

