## 5 STUDY OUTCOMES

### 5.1 Primary Outcome

| Outcome                                                                     | Measurements                                                                                                          |
|-----------------------------------------------------------------------------|-----------------------------------------------------------------------------------------------------------------------|
| Time (days) without readmission to hospital within 6 months after discharge | Patient records tracking (patient questionnaires and/or calls, GP records, hospital records); consecutive calculation |

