### 10.2 Recording and Assessment of Serious Adverse Events

Safety outcomes (readmission, ED visits, GP encounters, death) form an integral part of the study design and will be collected retrospectively at all follow up stages (1, 3 and 6 months after the intervention).

A possible causal dependence of individual SAEs on the study intervention will be assessed by the study team according the following definitions:

|                   |                                                                                                                                                                                                                                                 |
|-------------------|-------------------------------------------------------------------------------------------------------------------------------------------------------------------------------------------------------------------------------------------------|
| Unrelated: | 

• The event started in no temporal relationship to the medical intervention applied and

• The event can be definitely explained by underlying diseases or other situations.

             |
| Related:   | 

• The event started in a plausible temporal relationship to the medical intervention applied and

• The event cannot be definitely explained by underlying diseases or other situations.

 |

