#### 11.3.1 Datasets to be Analyzed, Analysis Populations

The analyses of primary and secondary outcomes will follow the intention-to-treat principle. Per-protocol analyses will be performed within the scope of sensitivity analyses. In the intervention group we will carry out exploratory analyses to identify factors related to drug deprescription.

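### Section 9.2.5 ends outcome recording for patients who stop without withdrawing consent, which conflicts with sections 7.4 and 9.2.1 and loses readmission and death data that records could supply

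*Protocol*

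**What the plan says.** Section 9.2.5 opens with a rule for two kinds of leaver joined by an or: "Patients who withdraw their consent or prematurely stop the study for subjective reasons will remain in the care of their attending GPs". It then closes data collection for both: "No further safety outcomes will be recorded within the study".

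The protocol's safety outcomes are largely its efficacy outcomes. Section 10.2 states: "Safety outcomes (readmission, ED visits, GP encounters, death) form an integral part of the study design". Section 9.2.4.1 adds: "Inpatient treatment and death are assessed within this study as primary or secondary outcomes, respectively, and will be recorded retrospectively". The primary outcome in section 5.1 is "Time (days) without readmission to hospital within 6 months after discharge", and its listed source is "Patient records tracking (patient questionnaires and/or calls, GP records, hospital records); consecutive calculation". For death, section 5.2 lists GP and hospital records only.

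Other sections treat leavers and non-responders differently:

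- Section 7.4 discontinues individual follow-up for a patient who withdraws consent. It names no other reason and notes that the intervention is given once.
- Section 9.2.1 deals with missing replies: "In case of outstanding responses the study team will contact" the patient first, then relatives, GPs or hospitals. Sections 8.3 and 9.2.2 make similar provision.
- Section 11.3.1 states: "The analyses of primary and secondary outcomes will follow the intention-to-treat principle". Section 11.3.2 compares the primary outcome by Kaplan-Meier and log rank.
- Section 11.4 plans a comparison of dropout rates and reasons between arms, multiple imputation, and a complete-case sensitivity analysis.

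**The concern.** When consent is withdrawn, ending data collection is legitimate. Section 9.2.5 applies the same ending to people who have not withdrawn consent, and it does not define the reasons that put a patient in that group. Because safety outcomes here include readmission and death, the sentence closes the primary endpoint for these patients as well as safety reporting.

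The log-rank comparison relies on censoring being unrelated to prognosis within each arm. The intervention consists of medication changes, so a patient who is unhappy with those changes might decide to stop. If such patients are also more likely to be readmitted, and if more of them leave from one arm, censoring them at exit distorts the comparison and can hide harm. Analysis cannot recover events that were never collected, so this has to be settled in the data-collection rule.

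**Working it through.** **1. The sections side by side**

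| Patient's situation | Section | Outcome data afterwards |
|---|---|---|
| Withdraws consent | 7.4, 9.2.5 | End |
| Does not reply at 1, 3 or 6 months | 8.3, 9.2.1, 9.2.2 | Pursued; 9.2.1 and 9.2.2 go on to relatives, GPs and hospitals |
| Stops without withdrawing consent | 9.2.5 | End |
| Stops without withdrawing consent | 7.4 | No rule ending follow-up |

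The last two rows conflict. The third row also sits badly beside the second, because the same records exist for both patients.

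**2. Reproducing the plan's sample size**

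Inputs from section 11.2: hazard ratio 0.80, two-sided alpha 0.05, power 80%, ICC 0.02, 50 patients per cluster, 40% censoring.

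- Events (Schoenfeld): 4 × (1.960 + 0.842)² / (ln 0.80)² = 630.5, rounded up to 631.
- Patients before clustering: 631 / 0.60 = 1,052.
- Design effect: 1 + 49 × 0.02 = 1.98.
- Patients after clustering: 1,051.7 × 1.98 = 2,082, or about 1,041 per arm. This rounds up to 21 clusters of 50, giving 1,050 per arm and 2,100 in total, as stated.
- Expected events: 2,100 × 0.60 = 1,260.

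**3. Power if some events are recovered**

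Power = Φ( √(d / (4 × 1.98)) × |ln 0.80| − 1.960 ), where d is the number of events.

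| Events d | Power |
|---|---|
| 1,260 (plan) | 80.4% |
| 1,280 (20 recovered, assumed) | 81.0% |
| 1,300 (40 recovered, assumed) | 81.6% |

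**4. The ceiling**

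With the stated medians, the proportions event-free at 182.6 days are 2^(−182.6/92.7) = 25.5% and 2^(−182.6/116.8) = 33.8%, mean 29.7%. The gap to 40% is 10.3 points, or about 217 of 2,100 patients. If every one of these were recovered, events would be 2,100 × 0.703 = 1,476 and power 86%. This gap holds all non-administrative censoring, so it is a ceiling and does not measure this rule.

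**5. Direction and size of bias (illustrations with assumed rates)**

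(a) Assume no effect of the intervention apart from the stoppers, who leave at day 30 and have twice the hazard from discharge onwards. The entries are ratios of event rates, intervention to control.

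| Stop, control v intervention | Full follow-up | Censored at exit |
|---|---|---|
| 5% v 15% | 1.066 | 1.028 |
| 2% v 5% | 1.019 | 1.008 |

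The standard error of the log hazard ratio is √(4 × 1.98 / 1,260) = 0.079. The larger shift is ln(1.066/1.028) = 0.036, or 0.46 of a standard error.

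(b) Assume that a share of patients in both arms deteriorates during the first three months, after which their hazard rises k-fold. Those in the intervention arm leave at that point and controls stay. The true hazard ratio is 1.0. Simulated Cox hazard ratios after censoring at exit:

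| Share deteriorating | k = 1 | k = 2 | k = 3 | k = 5 |
|---|---|---|---|---|
| 5% | 1.00 | 0.98 | 0.97 | 0.96 |
| 10% | 1.00 | 0.96 | 0.94 | 0.93 |
| 20% | 1.00 | 0.92 | 0.89 | 0.86 |

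With k = 1, leaving carries no prognostic information and there is no bias. Scenario (b) is deliberately extreme, since all the leaving is in one arm.

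**The case against.** The strongest reply is that the affected group may be nearly empty. The intervention is given once, so no treatment is left to stop. A patient who declares that they are stopping leaves only data collection, which is hard to tell from withdrawing consent. On that reading section 9.2.5 loosely restates section 7.4. The point about numbers stands: the group may be small. The point about wording does not, because 9.2.5 names the two groups separately and never says that the second has withdrawn consent.

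Three stronger readings are tempting and should not be drawn.

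- A reader might infer that patients too ill to return forms are lost. They are not: sections 8.3, 9.2.1 and 9.2.2 provide for pursuing missing replies.
- A reader might infer that the rule costs the trial about 217 patients' events, or the difference between 80% and 86% power. That gap also has to hold deaths, true losses, valid withdrawals of consent and the dropouts among physicians that section 7.4 places inside the 40%. The fix recovers none of these.
- A reader might infer that the hazard ratio will be biased. The documents give no stopping rate and no link between stopping and prognosis. Patients are not told which arm they are in, which makes a large difference in leaving less likely.

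Section 11.4 also deserves credit. Comparing dropout rates and reasons can reveal an imbalance. It cannot supply the missing events, and multiple imputation ordinarily assumes that leavers resemble stayers given what was observed. These measures mitigate the problem only in part.

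**Conclusion.** The point holds as an internal conflict with a modest and unknown effect. As written, section 9.2.5 discards obtainable primary and safety outcomes for patients who stop without withdrawing consent. That is at odds with sections 7.4 and 9.2.1 and weakens the intention-to-treat analysis.

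The loss of precision is probably small: about one percentage point of power if 20 to 40 events are at stake, a range that is assumed. Informative censoring is a risk and has not been shown to occur. It needs leaving to be related to prognosis and to differ between arms; if either is absent, the bias is small or nil. Every bias figure above rests on assumed rates. The case for change is that the correction is cheap and the lost data cannot be recovered later.

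**What to change.** In sections 9.2.5 and 7.4, limit the end of data collection to withdrawal of consent. Add a separate category for patients who stop questionnaires or contact but do not withdraw consent. For them, continue to collect readmission dates, death and ED visits to six months from the GP and hospital records already named in sections 5.1, 5.2 and 9.2.1, and keep them in the intention-to-treat analysis with that follow-up. Section 9.2.1 approaches the patient first, so for patients who have declined contact only the record sources should be used.

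Check that the patient information and consent form permits this. It is not among the documents at hand, so nothing is claimed about its present wording.

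The cost is an amendment to the wording, with ethics approval where required, and a small number of extra record requests of a kind already planned for non-responders.
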